### Clinical trial monitoring

This study will be subject to regular on-site monitoring visits by clinical monitors designated by the sponsor at the study hospitals. These visits are designed to ensure that the rights of participants in the clinical observations are safeguarded, that the data in the study records and reports are accurate and complete, and that the study adheres to the approved protocol, Good Clinical Practice (GCP) guidelines, and relevant regulations. This ensures that all aspects of the study protocol are strictly followed and that study documentation is accurately completed.

Investigators should truthfully, meticulously, and diligently record all items in the CRF in accordance with the requirements for completing the CRF, to ensure that the content of the CRF is genuine and reliable.

All observations and findings in the clinical observations should be verified to ensure the reliability of the data and to confirm that all conclusions drawn from the clinical observations are derived from the original data. Corresponding data management measures are in place during both the clinical observation and data processing stages.

### Quality control (QC)

Each research center will implement quality management of the study process, data and biological sample collection, and documentation archiving and study completion. Personalized quality management plans will be developed for each institution.

Quality control (QC) begins with the data entry system, and data QC checks will be run on the generated database. Any missing or abnormal data identified will be communicated to the trial institution for clarification or determination.

Monitors will verify, in accordance with written standard operating procedures (SOPs), whether the study is conducted in compliance with the protocol, International Council for Harmonisation of Technical Requirements for Pharmaceuticals for Human Use Good Clinical Practice (ICH GCP), and relevant applicable regulations [e.g., Good Laboratory Practice (GLP), Good Manufacturing Practice (GMP)], including the trial process, generation/ collection of data and biological samples, archiving (record-keeping), and reporting.

Clinical trial institutions will provide direct access to all study-related units, source data/documents, and reports for activities such as sponsor monitoring, auditing, or inspection by local regulatory authorities.

### Management of data and records collection and retention

Each participating institution shall comply with ICH GCP and relevant laws and regulations regarding the protection of participants' privacy and retain applicable medical and research records. Institutions should permit authorized representatives of the funder, sponsor, and regulatory authorities to inspect clinical records for quality assurance purposes (including photocopying as permitted by law), conduct reviews or audits, and evaluate the study's safety, progress, and data validity.

- - - 1. Responsibilities for data collection and management

Trial staff are responsible for data collection. Investigators should oversee their work and ensure the accuracy, completeness, legibility, and timeliness of the reported data. All source documents should be kept clear and tidy to ensure that the data can be accurately identified. The permanent copies of study visit records will be considered source documents for recording data of enrolled participants. Data entered into the electronic Case Report Forms (eCRFs) should be derived from the source documents and be consistent with the source data.

Clinical data [including AEs, concomitant medications, and data on expected drug AEs] and laboratory data will be entered into the database, which is provided by the data management center and complies with national regulations. The data system includes password protection and internal quality check functions, such as automatic range checks that can identify inconsistent, incomplete, or inaccurate data. Clinical data will be entered directly based on the source documents.

- - - 1. Retention of research data and records

The data of this study will be retained at the sponsor's institution for five years after the publication of the study results

### Protocol violation

Protocol violation refers to any non-compliance with the clinical trial protocol, the ICH GCP, or the Manual of Procedures (MOP). Non-compliance may arise from participants, investigators, or study center staff. In the event of deviations, corrective actions should be taken and completed promptly.

Investigators at the study centers are responsible for being vigilant about protocol violations. Upon identifying a violation, the investigator must report it in accordance with the Standard Operating Procedures (SOPs) for handling protocol deviations established by the local IRB and the clinical trial institution. All protocol violations must be documented in the source documents and submitted for review as required by the IRB. It is the investigator's responsibility to be aware of and comply with the relevant regulations of the IRB.

### Publication and Data Sharing Policy

After the completion of the study, the lead institution has the right to publish the summary report of this clinical observation in the form of a paper. Investigators from each participating institution and the sponsor are entitled to co-authorship of the paper.

### Conflict of interest policy

The study should not be influenced by any existing or foreseeable factors (such as pharmaceutical companies). Therefore, any individuals involved in the design, conduct, analysis, publication, or other aspects of this study will disclose and manage any actual conflicts of interest related to the study. Moreover, during the design and implementation of the study, individuals who may have conflicts of interest will be required to control such situations through appropriate methods.

1. **Adjustments to participating centers**: due to the slow enrollment rate at the originally planned number of centers (7 centers), the number of centers has been expanded to 10 centers for competitive enrollment, including Beijing HuiLongGuan Hospital (Beijing, China), Hebei Provincial Mental Health Center (Shijiazhuang, Hebei, China), Hunan Brain Hospital (Changsha, Hunan, China), Nanjing Brain Hospital (Nanjing, Jiangsu, China), Xiamen XianYue Hospital (Xiamen, Fujian, China), Shanxi Provincial Mental Health Center (Taiyuan, Shanxi, China), The First Affiliated Hospital of Zhejiang University (Hangzhou, Zhejiang, China), Xiangya Second Hospital of Central South University (Changsha, Hunan, China), The First Affiliated Hospital of Chongqing Medical University (Chongqing, China), The Fifth People's Hospital of Zigong City (Zigong, Sichuan, China).

**2. Adjustments to the dosing regimen:** The initial dosing regimen was based on the approved product label for schizophrenia, as no evidence-based guidelines for perospirone existed in MDD at the time of study design. However, due to differences in symptom profile, treatment goals, and anticipated tolerability between schizophrenia and MDD, the protocol was pragmatically adapted in clinical practice. Dosing was typically initiated at 4–8 mg/day (or <4 mg/day in older or milder patients), with titration guided by symptom severity and tolerability during the first two weeks; doses were generally stabilized by Week 2. The maintenance dose ranged from 4 to 24 mg/day and was administered once or twice daily. Higher doses (>24 mg/day) were used on a case-by-case basis for patients with more severe symptoms, always within the approved maximum of 48 mg/day. All adjustments were made under the supervision of experienced clinicians.

**3. Adjustments to sample size calculation:** The sample size was finally calculated based on previous studies of SGA adjunctive therapy in patients with MDD, which reported response rates ranging from 10.5% to 58.9% in the SGA group and from 6.8% to 46.3% in the placebo group. The pair of groups showing the largest difference in response rates (46.6% vs. 26.6%) was selected as the basis for sample size estimation. A Chi-square test was performed using Power Analysis and Sample Size (PASS) software, version 21.0.3, to determine the required sample size. With a two-sided alpha level of 0.05 and 80% power (β = 0.2), a total sample size of 176 participants (88 per group) was estimated to detect a statistically significant difference in the primary efficacy outcome. To account for an anticipated dropout rate of 10%, the initial sample size was increased to 196 participants (98 per group). Given the possibility of a higher-than-expected dropout rate, the final sample size was further adjusted to 210 participants (105 per group), which also provides sufficient power to detect a significant difference in remission rates (36.8% vs. 18.9%) under the same statistical assumptions.

**4. Adjustments to efficacy end points**: the primary efficacy end points were the MADRS response rate (defined as an improvement of ≥50% in the MADRS score from baseline) and remission rate (defined as a MADRS score of ≤10) at the end of treatment (week 8). The secondary efficacy end points were the response and remission rates at week 4, and the scores reductions of the scales mentioned in the protocol at each visit point.

**5. Adjustments to statistical methods**: Efficacy analyses were performed in the FAS. Prior to initiating the analysis of efficacy outcomes, Breslow-Day test was carried out to assessed whether there was any centre effect that contributed to the results in the multi-centre trial.

For the primary efficacy outcomes and partial secondary efficacy outcomes (i.e. response and remission rates at weeks 4 and weeks 8), last observation carried forward (LOCF) method was used to handle the missing data in the anaysis of these outcomes. Since these outcomes were defined based on MADRS scores at the corresponding visit (response: ≥50% reduction from baseline; remission: MADRS score ≤10), missing MADRS values in the FAS were imputed using LOCF, and response or remission status was subsequently determined based on the imputed scores. Logistic regression models were employed to analyze and compare these outcomes between the the perospirone + SSRIs/SNRIs group (perospirone group) and the placebo + SSRIs/SNRIs group (placebo group), using results of the placebo group as reference. In the logistic regression model, treatment group was included as factor, and baseline MADRS total score was included as a covariate.

For the other secondary efficacy measures, the mean change of the included scales (MADRS, QIDS-SR16, HAMA, and Q-LES-Q-SF) from the baseline (Week 0) to Week 4 and Week 8 were analyzed. The mean changes and the differences of the mean changes of the secondary efficacy outcomes between the perospirone group and the placebo group were calculated and compared through the use of a mixed model for repeated measures (MMRM) analysis (with an unstructured covariance matrix). This method is widely recommended for longitudinal data with missing values under the missing at random (MAR) assumption, as it utilizes all available data and does not require explicit imputation. The model included the baseline total scores of each scales, study centre (centre 1 to centre 10), treatment group (perospirone and placebo), time (week 2, week 4 and week 8), and time-by-treatment interaction as fixed effects, with the subjects-specific effects as a random effect. The least squares mean (LSM) changes of the scores for the two groups were reported.

Chi-square tests or Fisher’s precision probability tests were conducted to compare the overall incidence rates of AEs, SAEs and AEs leading to treatment discontinuation, as welll as the incidence rates of each drug related-AE between the two groups. All statistical analyses were done in Statistical Analysis System (SAS) version 9.4. Statistical significance was determined by a two-sided p value less than 0.05

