| Study population | Screening population: 248  Number of patients to be included in the study: 210 (105 per study arm).  The actual number of patients included: 210 (108 in the perospirone group and 102 in the placebo group)  Number drop outs: 43 (23 in the perospirone group and 20 in the placebo group)  Number of patients to be evaluated: 177 in mITT (FAS) evaluation (87 in the perospirone group and 90 in the placebo group), and 167 with complete follow-up (85 in the perospirone group and 82 in the placebo group) |
| Inclusion criteria | - Meeting Diagnostic and Statistical Manual of Mental Disorders, Fifth Edition (DSM-5) criteria for MDD, confirmed by the Mini International Neuropsychiatric Interview (MINI); - The current episode duration of MDD must be ≤1 year; - Failed to respond adequately to at least one kind of antidepressant at therapeutic doses for at least 4 weeks, as indicated by a current score of at least 20 on the Montgomery-Asberg Depression Rating Scale (MADRS); - Aged 18 ~ 60 years; - Education >= 6 years and able to complete the cognitive tests; - Having the ability to understand and sign a written informed consent form prior to participation in any screening procedures. |

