**B.Secondary efficacy end points:**

1. .Reduction rates in MADRS and Hamilton Anxiety Scale (HAMA) scores at each visit.

2. Change rates in each Clinical Global Impression (CGI) and Beck Suicidal Ideation Scale (BSI-CV) subscales scores at each visit.

3. Reduction rates in Pittsburgh Sleep Quality Index (PSQI), 16-item Quick Inventory of Depressive Symtomatology-Self-Report (QIDS-SR16), Generalized Anxiety Disorder 7-item Scale (GAD-7), and Snaith-Hamilton Pleasure Scale (SHAPS) scores at each visit.

4. Change rates in Sheehan Disability Scale (SDS) and Quality of Life Enjoyment Questionnaire - Short Form (Q-LES-Q-SF) scores at each visit.

5. Change rates in neurocognitive function test performance before and after treatment.

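### Section 12 contradicts itself on the secondary endpoints: item 4 keeps every protocol scale at each visit, while item 5 lists four scales at weeks 4 and 8, without reason or date

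*Protocol*

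**What the plan says.** Three parts of the protocol bear on which secondary outcomes are analysed.

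- **Endpoint lists (Sections 1.1, 3, 8.1.2 and 9.2.2).** Section 9.2.2 names ten rating scales as secondary endpoints. For clinician-rated depression and anxiety the entry is "Reduction rates in MADRS and Hamilton Anxiety Scale (HAMA) scores at each visit". For global impression and suicidal ideation it reads "Change rates in each Clinical Global Impression (CGI) and Beck Suicidal Ideation Scale (BSI-CV) subscales scores at each visit". The entry that also covers sleep and self-rated depression ends with "Generalized Anxiety Disorder 7-item Scale (GAD-7), and Snaith-Hamilton Pleasure Scale (SHAPS) scores at each visit". The section adds change in neurocognitive test performance. Section 3 specifies the cognitive part as five tests plus the PDQ-D.
- **Section 9.2.4.** This gives an MMRM for secondary outcomes in general. The detail beneath it names MADRS, HAMA, SDS, Q-LES-Q-SF, QIDS-SR16 and GAD-7.
- **Section 12 (adjustments during the trial).** Item 4 makes week-4 response and remission secondary, together with "the scores reductions of the scales mentioned in the protocol at each visit point". Item 5 then says what was done for the remaining secondary measures: the outcome is "the mean change of the included scales (MADRS, QIDS-SR16, HAMA, and Q-LES-Q-SF"). Only two time points are listed for it, weeks 4 and 8. The MMRM in item 5 nevertheless has "time (week 2, week 4 and week 8") as its time factor.

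The synopsis (Section 1.1) of the same document already reports the outcome of recruitment: "The actual number of patients included: 210 (108 in the perospirone group and 102 in the placebo group"), with 43 dropouts and 177 patients in the FAS.

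**The concern.** Items 4 and 5 stand next to each other in the current text and describe two different sets of secondary results. A reader following item 4 expects every scale at every visit. A reader following item 5 expects four scales at two visits. Item 5 gives no criterion for the four, no reason and no date.

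Two things are at stake. If item 5 governs, the protocol's own objectives on sleep, anhedonia, suicidal ideation with global impression, and cognition go without a planned analysis in Section 12. This is despite Sections 2.1 and 2.2.2, which argue for the drug partly on sleep and cognition. Second, when a trial collects many scales and reports a few without a stated rule, the reader cannot tell whether the missing ones were null, adverse or never analysed. That is the usual route to selective reporting, whatever the intention.

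**Working it through.** The protocol states no figure for this point, so the check is a count of its own lists against each other.

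**Step 1. Rating scales.** From Section 9.2.2: MADRS and HAMA (2), CGI and BSI-CV (2), PSQI, QIDS-SR16, GAD-7 and SHAPS (4), SDS and Q-LES-Q-SF (2). Total 2 + 2 + 4 + 2 = 10. Item 5 of Section 12 names 4. Omitted: 10 − 4 = 6 (CGI, BSI-CV, PSQI, GAD-7, SHAPS, SDS). Also omitted are the five cognitive tests and PDQ-D.

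**Step 2. Objectives.** The seven secondary efficacy objectives in Section 8.1.2, set against item 5:

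| Objective | Instruments | In item 5 |
|---|---|---|
| Depressive symptoms | MADRS, QIDS-SR16 | both |
| Anxiety | HAMA, GAD-7 | HAMA only |
| Sleep | PSQI | none |
| Anhedonia | SHAPS | none |
| Suicidal ideation and global impression | BSI-CV, CGI | none |
| Quality of life and functioning | SDS, Q-LES-Q-SF | Q-LES-Q-SF only |
| Cognition | five tests (PDQ-D added in Section 3) | none |

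Result: 4 of 7 with no scale, 2 of 7 half covered, 1 of 7 fully covered.

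**Step 3. Scales by visit.** In the Section 1.3 schedule, seven of the ten scales are taken at weeks 2, 4 and 8 (7 × 3 = 21). SHAPS, SDS and Q-LES-Q-SF are taken at weeks 4 and 8 only (3 × 2 = 6). Total 21 + 6 = 27 post-baseline scale-visits. Item 5 lists 4 × 2 = 8, and 8/27 = 30%. If the week-2 estimates that the item 5 model can also yield for MADRS, QIDS-SR16 and HAMA are counted, the figure is 8 + 3 = 11, and 11/27 = 41%.

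**Step 4. Week 2.** Week 2 is a level of the model's time factor, but change to week 2 is not among the results that item 5 lists. Q-LES-Q-SF has no week-2 measurement in the schedule, so the stated three-level time factor does not fit one of the four scales.

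**Step 5. Section 9.2.4 as a third version.** Its general model would cover any secondary outcome. Its detail names six of the ten rating scales. CGI, BSI-CV, PSQI and SHAPS are not named there, nor is cognition, and sleep and anhedonia are to be judged from QIDS-SR16 and GAD-7. Section 12 does not say whether this text still applies.

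**The case against.** The strongest reply is that the omitted scales do have an analysis elsewhere. Section 9.2.4 gives a general MMRM for secondary outcomes and names SDS and GAD-7, and Section 12 presents itself as adjustments to the original protocol without withdrawing that model. This stands in part. A reader might infer that every instrument outside item 5 is without any analysis in the document, and Section 9.2.4 does not support that. What remains is that Section 12, the later text, gives a closed list that conflicts with its own item 4. A separate SAP could hold further analyses, but it could not remove a conflict between two items of the protocol.

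A reader might also infer that the week-2 comparisons have been abandoned. They have not: week 2 and its interaction with treatment are in the item 5 model, so the week-2 contrasts for MADRS, QIDS-SR16 and HAMA can be estimated. Only their place in the reported results is unclear.

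Third, a reader might infer from the past tense and the final counts that the four scales were picked for their results. The document does not show this. The counts stand in the synopsis, not in Section 12, and they are not efficacy data. Section 4.6.2 places unblinding after CRF verification, and the choice of scales carries no date. What can be said is that the choice is unexplained and that nothing in the document excludes influence from the data.

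Finally, the cognitive tests and PDQ-D, measured only at baseline and week 8, fit item 4's reference to scales at each visit poorly. For that reason the main count rests on the ten rating scales, and cognition is stated separately.

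**Conclusion.** The contradiction holds on current text and does not depend on superseded wording. Item 4 keeps all protocol scales at each visit; item 5 names 4 of the 10 rating scales, at weeks 4 and 8, and no cognitive outcome. Within Section 12, 4 of the 7 secondary efficacy objectives have no analysis and 2 are half covered. The primary endpoints and the safety analyses are not affected.

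The counts assume that Section 9.2.2 is the intended list of rating scales and that Section 1.3 gives the visits. They describe Section 12 only. With Section 9.2.4 read alongside, the position is three unreconciled versions, not an absence of any analysis. Outcome selection is a risk left open by the missing date and reason; it is not demonstrated.

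**What to change.** Reconcile Section 12 items 4 and 5 with Section 9.2.4 into one list of secondary scales and visits, and say expressly whether Section 9.2.4 still applies.

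Analyse and report every listed scale with the existing MMRM at the visits where Section 1.3 collects it. That means weeks 2, 4 and 8 for seven scales, and weeks 4 and 8 only for SHAPS, SDS and Q-LES-Q-SF, with the time factor set to match. For the cognitive tests and PDQ-D, which have one post-baseline assessment, use a baseline-adjusted ANCOVA at week 8. Confirm first that PDQ-D was taken at week 8: the schedule's cognitive footnote includes it, but the Visit 3 description in Section 8.3 does not name it.

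State when the four scales were singled out relative to unblinding, and why. If they remain the main secondary scales, label the others exploratory and still report them.

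The schedule already calls for these data, so the cost is more runs of an existing program, a longer results table and a less concise message.
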